**Methods/design:**

Thirty-six private practitioners will be included in three treatment centers and randomly designated to either training in manualized CBT or no specific training. The treatment effects of the therapies conducted by both groups of therapists will be compared. A total of 162 patients (*n* = 116 completers; *n* = 58 per condition) will be enrolled. Liebowitz Social Anxiety Scale (LSAS) will serve as primary outcome measure. Remission from social phobia is defined as LSAS total ≤30 points. Data will be collected at treatment begin, after 8, 15, and 25 sessions (50 min each), at treatment completion, as well at 6 and 12 months post-treatment.

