## Methods/design

### Study centers

The present study is being conducted by three trial sites, namely the Universities of Dresden ([name]. [name]), Frankfurt ([name]. [name]), and Göttingen ([name]. [name]), each coordinating at least 12 private practices.

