### Sample size calculation

The only study directly comparing performance of therapy delivered under RCT conditions and routine care refers to group CBT for social phobia
[18] and showed a small but significant advantage for the RCT therapies. The difference between the Clark trials
[17,18] and other controlled trials suggests a much higher difference in the to-be expected between-group effect sizes of our study but only under the improbable assumption that trained private practitioners will be comparably successful as the specialized therapists in the Clark trials. Sholomskas *et al.*[39], in a study directly testing the effects of additional training, but not in the field of SP, reported an average between group effect size of d = 0.69 when comparing therapists who were trained in a seminar plus supervision and therapists who used a manual without further training with regard to their performance in standardized role plays. However, this estimation does not directly refer to the expected effect sizes for the therapeutic benefit, which is the main outcome criterion of this trial. Given this inconsistent information, we choose to expect a more conservative effect size of d = 0.50 between Group 1 (trained therapists) and Group 2 (treatment-as-usual), for pragmatic reasons. We aimed at estimating the sample size needed for a dichotomous approach (remission rates according to the above defined criterion, LSAS <30). In order to assure comparability with the parallel trial for psychodynamic therapy
[37] we introduced the same conservative assumptions: (1) the ICC was set to 15% which is high compared to similar studies
[40]; and (2) for the primary analysis (ITT) drop-outs will be analyzed as patients with no remission. When assuming <50% remitters and an equal drop-out rate in both conditions, the absolute difference between remission rates will remain unchanged, but the relative difference will be much greater and will substantially enlarge the difference between treatments.

In contrast to Wiltink *et al.*’s study protocol
[37], the average number of patients in a cluster was assumed to be five, as we choose to collaborate more continuously with the included therapists. Please note that this is the only assumption differing from those made in
[37] resulting in a higher *a priori* sample size than in
[37].

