In order to detect a difference between Groups 1 and 2 at α = 0.05 (one-tailed; see Discussion) with a power of 0.80, *n* = 58 patients per group are required according to the formula of Campbell *et al.*[40,41] for cluster-randomization, given that five patients per therapist will be treated (for a more comprehensive account, see
[42]):

$$N=2*{\left[\frac{\sigma (z_{\alpha }+z_{\beta })}{E}\right]}^{2}*\left[1+(m-1)\rho \right]=2*{\left[\frac{\left(z_{\alpha }+z_{\beta }\right)}{ES}\right]}^{2}*\left[1+(m-1)\rho \right]$$

(z_α_, z-value for probability of error type I alpha; z_β_, z-value for probability of error type II beta; σ, standard deviation of outcome; E, expected ES of outcome; m, mean observations for each cluster; ρ, Intracluster correlation coefficient (ICC); ES = E/σ, standardized effect size)

Given a conservative drop-out rate estimate of 25% (taking into account slightly elevated drop-outs in a practice study), a total of *n* = 162 patients are required to be allocated to the trial. Thus, *n* = 54 patients will have to be included in each center. According to data of the [name] *et al.*[43] study on social phobia, in which patients were recruited in a comparable setting of German psychotherapeutic care, 61% of 250 patients meeting the inclusion criteria can expected to be finally included. We estimate that not more than about 250 patients will have to be assessed for eligibility.

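### The sample size section pairs five patients per therapist with 58 completers per group; the trial's own counts give 4.5 or 3.2 per therapist, and at none of these does the printed formula give 58.

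*Protocol article*

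**What the plan says.** The Sample size calculation section states that "the average number of patients in a cluster was assumed to be five", calls this the only assumption that differs from the parallel psychodynamic trial, and repeats it beside the result: "given that five patients per therapist will be treated". The formula printed there defines m as the mean number of observations in a cluster. The other inputs are a one-tailed alpha of 0.05, a test "with a power of 0.80", d = 0.50 and an intracluster correlation of 0.15 ("the ICC was set to 15% which is high compared to similar studies"). The result is 58 per group, raised to 162 in total for drop-out.

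The therapist and patient counts stand elsewhere. The abstract says "Thirty-six private practitioners will be included in three treatment centers", with 162 patients enrolled, of whom 116 (58 per condition) are completers. Study centers describes the three sites as "each coordinating at least 12 private practices", so 36 is a minimum. Participants and Sample size calculation both give 54 patients per centre. Sample size calculation also says that the primary intention-to-treat analysis counts drop-outs as not remitted, so all enrolled patients are analysed.

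**The concern.** The therapist is the randomised unit, so the number of therapists and the patients per therapist determine the precision. The cluster size is also the one input chosen specifically for this trial. Yet 36 therapists with five patients each would treat 180 patients, not 162, and certainly not 116.

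The deeper difficulty is that two bases are combined. The 58 per group is a completer count, because drop-out is added afterwards and the abstract labels it so. A cluster size near five can be reached only by counting everyone enrolled. The primary analysis is on everyone enrolled, which is neither 58 per group nor five per therapist. A reader cannot tell which combination of therapists, cluster size and patients the stated 0.80 belongs to, and it is fair to ask whether it belongs to any of them.

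**Working it through.** **Inputs** (protocol article): one-sided alpha 0.05, z = 1.645; power 0.80, z = 0.842; ES = 0.50; ICC = 0.15; m = 5; 36 therapists; 162 enrolled; 116 completers.

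**1. The plan's own figure.** The formula is N per group = 2 × [(z_α + z_β)/ES]² × [1 + (m − 1) × ICC].
- Without clustering: 2 × (2.4865/0.50)² = 49.46.
- Design effect at m = 5: 1 + 4 × 0.15 = 1.60.
- N = 49.46 × 1.60 = 79.1, so 80 per group. The stated 58 is not reproduced.
- Working back, 58/49.46 = 1.17. That design effect corresponds to m = 1 + 0.17/0.15, or about 2.15 before rounding.
- Two-sided alpha gives 100.5, and a t-based one-sided n of 51 gives 81.6. Neither recovers 58.

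**2. Cluster size from the trial's counts.**
- Enrolled: 162/36 = 4.5.
- Completers: 116/36 = 3.22.
- At five each: 36 × 5 = 180 patients.
- More than 36 therapists with 162 patients would make the mean smaller still.

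**3. Required n and power at each cluster size.** Power is Φ(0.50 × √(n/(2 × DE)) − 1.645), where DE is the design effect.

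| m | DE | n needed per group | Power, 58 per group | Power, 81 per group |
|---|---|---|---|---|
| 5 | 1.60 | 79.1 → 80 | 0.69 | 0.81 |
| 4.5 | 1.525 | 75.4 → 76 | 0.70 | 0.82 |
| 3.22 | 1.333 | 65.9 → 66 | 0.75 | not applicable |

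The last cell is left out because 3.22 per therapist belongs to completers and 81 per group to all enrolled. With a t reference on 34 degrees of freedom (36 therapists less two), 0.82 becomes 0.81 and 0.75 becomes 0.74.

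**4. Unequal clusters.** Patients choose their therapist, so cluster sizes will vary. The documents give no coefficient of variation (CV), so I assume 0 to 0.5. DE = 1 + [(1 + CV²) × 4.5 − 1] × 0.15 gives 1.525 at CV 0, 1.60 at 0.33 and 1.69 at 0.5. At 1.69 the power is about 0.66 with 58 per group and 0.79 with 81.

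**5. Drop-outs as non-remitters.** Suppose d = 0.50 describes completers and a quarter of each arm is set to non-remission. The difference in remission proportions is then 0.75 times its completer value. As an illustration, assume completer remission of 0.30 in the control group; an arcsine effect size of 0.50 then means 0.544 in the trained group. Multiplying both by 0.75 gives 0.225 and 0.408, an effect size of 2 × (arcsin √0.408 − arcsin √0.225) = 0.40. Power with 81 per group at m = 4.5 is then about 0.66. Assumed control rates of 0.20 and 0.40 give 0.68 and 0.63.

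**The case against.** The strongest reply is that five is a planning average, and that 4.5, the count relevant to the intention-to-treat analysis, is close to it. At a fixed ICC a larger m only raises the required n, so the choice is cautious: 80 against 76 per group. It may even be apt, because a mean of 4.5 with an assumed CV of 0.33 has the same design effect as five equal patients per therapist. All of this stands. Taken alone, the mismatch in m is a minor inconsistency.

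It does not rescue the 58. The caution claimed for m = 5 never reached that figure, which carries a design effect of about 1.17 instead of 1.60.

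Two stronger readings are tempting. A reader might infer that the wrong cluster size leaves the trial too small. It does not: putting m right lowers the required n. A reader might also infer that centres would recruit to different targets, 60 or 54. The documents do not support that: the only centre target given is 54, five appears only as a planning input, and patients choose their therapist with no quota set. Nor is there any reason to read 180 as an intended patient total.

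**Conclusion.** The point holds as a mixing of bases that hides an unsupported power statement. The gap in cluster size is small and conservative on the intention-to-treat basis. What matters is that 58 per group does not deliver 0.80 at any cluster size the documents support. Power is about 0.69, 0.70 or 0.75 at m = 5, 4.5 or 3.2, against requirements of about 80, 76 or 66.

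The planned enrolment may still suffice. All 81 per arm analysed at 4.5 per therapist give about 0.82. That rests on d = 0.50 and ICC 0.15 as stated, 36 therapists split equally, near-equal cluster sizes, and d = 0.50 applying to the rates after drop-outs are set to non-remission. The plan argues that the absolute difference is unaffected by this rule. If d = 0.50 describes completers instead, the difference shrinks and the 0.82 does not hold. The documents do not settle which is meant, so they do not show that the trial as a whole is underpowered.

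**What to change.** In Sample size calculation, choose one basis and state it in a single line. For the intention-to-treat analysis of all 162 patients this is 18 therapists per arm, a mean of 4.5 patients per therapist and 81 patients per arm.

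Then restate the power on that basis, about 0.82, and say explicitly that d = 0.50 is assumed to hold with drop-outs counted as non-remitters. If 58 completers per group is kept as a supporting figure, give it with 3.2 patients per therapist and a power of about 0.75. If m = 5 is kept as a deliberate margin for unequal clusters, say so and give about 80 per group as the requirement.

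The cost is a few restated figures, with no extra patients or therapists. The downside is that the stated power for 58 per group becomes less favourable, and unequal cluster sizes would lower it somewhat further.

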### Participants

Patient inclusion and exclusion criteria are listed in Table
1. The sample fulfilling these criteria are considered representative for social phobia patients qualifying for treatment in an outpatient setting. Assuming a drop-out rate of 25% over a period of 2 years, a total of 162 patients are planned to be enrolled in the study (that is 54 patients in each center; see sample size calculation). Patients will only be able to enrol once in the present trial. Participants will be able to directly contact the trial centre in response to advertisements via the internet, flyers, or newspaper articles. Alternatively, they will be referred to by healthcare practitioners (that is, medical doctors or private practitioners in psychotherapy). Once the diagnostician confirms the patient’s eligibility for the study, the patient will select and contact a therapist from a list of candidates for treatment. Only private practitioners officially listed in the German chambers of psychotherapists will be recruited. Informed consent from both the therapist and the patient will be collected. All therapists will have to be certified in CBT. Inclusion criteria for therapists are broad (that is, any age and gender, living in the area of the trial center) as a function of the naturalistic aspects of the present trial. However, practitioners having recent training (within the last 5 years) in the Clark and Wells treatment of SP
[17] will be excluded from the study. Measures of allegiance to the treatment condition and professional experience will be collected via self-report of the therapists as well as via expert ratings of video-documented sessions.

**Table 1 T1:** Inclusion and exclusion criteria

**Inclusion criteria**	Diagnosis of SP (SCID-I)
	Liebowitz Social Anxiety Scale >30 (>60 for generalized subtype)
	Age 18 to 70 years
	SP must be primary diagnosis (most severe disorder according to ADIS-IV)
	SP patients with co-morbid disorders will be included, provided that SP is the primary diagnosis, thus ensuring a clinically representative sample as well as analyses of subgroups (for example, type of SP, patients with co-morbid depressive disorder)
**Exclusion criteria**	Psychotic disorder
	Prominent risk of self-harm
	Acute substance-related disorders
	Personality disorders except for avoidant
	Obsessive-compulsive or dependent personality disorder (SCID-II) organic mental disorder
	Severe medical conditions

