### Randomization

Therapists will be randomly assigned either to a training group (manualized CBT), in which they will undergo an intensive training of the treatment manual for social phobia, or to a control group (routine care), in which the non-manualized CBT standard treatment is applied. Private practitioners will be block randomized. Practitioner randomization will be stratified for each trial center using the nQuerie Advisor® 6.01 software program
[44]. As participants in a naturalistic study, patients are not randomized and have no knowledge on whether or not the therapist they have freely chosen has been trained in manualized CBT. Diagnostic procedures are performed by independent, blinded, and specially trained assessors for diagnosis and observer-rated outcome measures. All diagnosticians are trained by one of the co-authors (US), who was responsible for quality assurance of CBT in the SOPHO-NET study and has extensive experience in conducting RCT of SP
[43,45]. There will be multimethod assessment of specific and non-specific therapy outcome including both patient and assessor perspective; control for drop-outs, intent-to-treat analyses. Generalizability of results will be established by above defined inclusion and exclusion criteria (Table
1) and by the multicenter approach.

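### The design effect makes no allowance for unequal numbers of patients per therapist although patients choose their therapist; under chance variation this costs about 3 to 4 power points

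*Protocol article*

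**What the plan says.** The Sample size calculation section of the protocol article plans for "α = 0.05 (one-tailed; see Discussion) with a power of 0.80". On the effect it says "we choose to expect a more conservative effect size of d = 0.50", and on clustering "the ICC was set to 15% which is high compared to similar studies". For cluster size, "the average number of patients in a cluster was assumed to be five", and the requirement of 58 per group is stated "given that five patients per therapist will be treated". The formula multiplies the unclustered n by 1+(m−1)ρ, where m is "m, mean observations for each cluster". No term describes how the number of patients varies between therapists.

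The abstract gives 36 therapists, 162 patients and 116 completers (58 per condition). Under Participants, once eligibility is confirmed, "the patient will select and contact a therapist from a list of candidates for treatment". The Randomization section adds: "As participants in a naturalistic study, patients are not randomized". The article describes no cap, quota or steering that would even out the numbers per therapist.

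**The concern.** The factor 1+(m−1)ρ is the exact variance inflation only when all clusters have the same size. When sizes vary, a therapist with many patients adds correlated observations that carry less independent information, and the inflation is larger than the mean size implies. Here the size of each cluster is the outcome of patient choice. Some variation is therefore expected even if no therapist is more attractive than another.

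What is at stake is the power statement. The section presents its assumptions as conservative, but leaving out this term makes the calculation less conservative. Correcting only the arithmetic for m = 5 would produce a new figure that still omits the loss.

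**Working it through.** **Inputs (all from the protocol article).** One-sided α = 0.05, power 0.80, d = 0.50, ICC ρ = 0.15 and m = 5 from Sample size calculation; 36 therapists (18 per arm if split equally), 162 enrolled (81 per arm) and 116 completers (58 per arm) from the abstract.

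**Step 1: the plan's own figure.** The unclustered n per arm is 2 × [(1.645 + 0.842)/0.50]² = 49.5. The design effect is 1 + 4 × 0.15 = 1.60. The product is 79.1, so about 79 to 80 per arm. The stated 58 is not reproduced; it would need a design effect of 58/49.5 = 1.17. Power is Φ(0.5 × √(n/(2·DE)) − 1.645). At n = 58 and DE = 1.60 it is 0.69, with perfectly equal clusters. That gap is a separate fault and is not caused by unequal clusters.

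**Step 2: how unequal clusters would be by chance.** If each patient picks one of k therapists with equal probability, CV² = (1 − 1/k)/m.
- m = 5, 79.1 patients per arm, k = 15.8: CV = 0.43.
- 81 per arm on 18 therapists, m = 4.5: CV = 0.46.
- 58 per arm on 18 therapists, m = 3.2: CV = 0.54 (0.55 if computed over all 36 therapists).

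**Step 3: design effect and power with m and CV matched.** The patient-weighted design effect is 1 + ((1 + CV²)m − 1)ρ. The mixed-model column divides the equal-cluster design effect by the relative efficiency 1 − CV²λ(1 − λ), where λ = mρ/(mρ + 1 − ρ).

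| Setting (per arm) | CV | DE, equal | DE, unequal | Power, equal | Power, patient-weighted | Power, mixed model |
|---|---|---|---|---|---|---|
| 79.1, m = 5 | 0.43 | 1.60 | 1.74 | 0.80 | 0.77 | 0.78 |
| 58 on 18 therapists | 0.54 | 1.33 | 1.475 | 0.754 | 0.716 | 0.728 |
| 81 on 18 therapists | 0.46 | 1.525 | 1.67 | 0.824 | 0.794 | 0.806 |

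The last row assumes that all enrolled patients are analysed and that d = 0.50 is not diluted by drop-outs. A simulation with 16 therapists and 80 patients per arm agrees with the first row: 0.804 with equal clusters, 0.773 patient-weighted and 0.785 with efficient weighting.

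**Step 4: sensitivity to CV.** Patient-weighted power at assumed values:

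| CV | 79.1, m = 5 | 58 on 18 | 81 on 18 |
|---|---|---|---|
| 0.3 | 0.785 | 0.742 | 0.811 |
| 0.6 | 0.744 | 0.708 | 0.773 |
| 0.8 | 0.704 | 0.676 | 0.736 |

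The CV values in this table are assumptions; the article gives no information from which to choose among them.

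**The case against.** The strongest objection is that equal-probability choice is a model and the article does not state it. Patients choose from a list, and private practices may have limited places. If full practices leave the list, sizes vary less than by chance. An illustrative simulation of 162 patients on 36 therapists gave a CV of about 0.40, 0.34 and 0.20 with limits of 7, 6 and 5 patients per therapist. This stands: the chance CV is a baseline, and an unstated intake limit would lower it just as unequal popularity would raise it.

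Second, the ICC of 0.15 is described as high. With m = 5 and CV 0.43, a true ICC of 0.6/(1.187 × 5 − 1) ≈ 0.12 would bring the design effect back to 1.60. That is a possible margin, but the article does not present it as an allowance for unequal clusters.

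Third, the loss depends on the analysis. The article plans logistic regression for remission, with no cluster weighting stated, and random effects models for the repeated measures, with no therapist effect specified. An efficient mixed model would lose under 2 points at m = 5. This also stands.

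Fourth, using a mean cluster size is a common planning approximation. That is fair, and it is why the point is one of allowance more than of calculation error. It does not answer the fact that the design itself generates unequal sizes.

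A reader might go further and infer that the CV cannot fall below about 0.5, or that unequal clusters pull power at 58 per arm to around 0.6. The documents support neither. The chance CV at m = 5 is about 0.43 and is not a lower bound. At 58 per arm and m = 5, power is already 0.69 with equal clusters, and chance variation takes it only to about 0.65. Lower figures need CVs that are assumed. A CV computed at 4.5 or 3.2 patients per therapist should also not be combined with m = 5.

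**Conclusion.** The point holds at a modest size. The stated power contains no allowance for unequal cluster sizes, although patient choice will produce them. Under equal-probability choice and a patient-weighted analysis the loss is about 3 to 4 points in each matched setting; with an efficient mixed model it is about 2 to 3 points, and under 2 at m = 5. The direction follows from the design. The size rests on the choice model, on ICC 0.15 and d = 0.50 as stated, and on an equal split of therapists between arms.

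It ranks below the discrepancy between 58 per arm and the 79 to 80 that the formula gives, which accounts for most of the shortfall at 58. It remains after that discrepancy is repaired.

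**What to change.** In the Sample size calculation section, replace the design effect with 1 + ((1 + CV²)m − 1)ρ. Take m and CV from the same setting: the 36 planned therapists with either the 116 completers or the 162 enrolled. Report power for both over a range of CV labelled as assumed, for example 0.3 to 0.8, and state any intake limit that applies. Do this together with reconciling 58 per arm with the formula.

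This changes a line or two of text. It needs no additional patients, no cap per therapist and no change to patient choice. The cost is that the stated power becomes slightly less favourable.

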### Randomization

Therapists will be randomly assigned either to a training group (manualized CBT), in which they will undergo an intensive training of the treatment manual for social phobia, or to a control group (routine care), in which the non-manualized CBT standard treatment is applied. Private practitioners will be block randomized. Practitioner randomization will be stratified for each trial center using the nQuerie Advisor® 6.01 software program
[44]. As participants in a naturalistic study, patients are not randomized and have no knowledge on whether or not the therapist they have freely chosen has been trained in manualized CBT. Diagnostic procedures are performed by independent, blinded, and specially trained assessors for diagnosis and observer-rated outcome measures. All diagnosticians are trained by one of the co-authors (US), who was responsible for quality assurance of CBT in the SOPHO-NET study and has extensive experience in conducting RCT of SP
[43,45]. There will be multimethod assessment of specific and non-specific therapy outcome including both patient and assessor perspective; control for drop-outs, intent-to-treat analyses. Generalizability of results will be established by above defined inclusion and exclusion criteria (Table
1) and by the multicenter approach.

